### **8.3.9 Facility Questionnaire and Dosimetry Audit**

All participating institutions must perform a Facility Questionnaire (FQ) that will collect information about the participating institution and about the methods to be applied for this specific study. The FQ will be reviewed by the RT-QA group.

These institutions must provide evidence for a successful implementation and usage of the RT technique which corresponds / is relevant to the treatment described by the protocol. Further, the implemented quality assurance strategies to ensure correct delivery of the treatment described by the protocol must be specified. In particular, QA procedures of the imaging system (e.g. CBCT) aiming to a coincidence between imaging and machine isocenter have to be provided. Details will be enquired in the FQ.

All participating centers must provide a valid External Dosimetry Audit (EDA) for the machine(s) planned to treat the study patients, which shall be not older than two years. An updated EDA shall be submitted once every two years.

### **8.3.10 Radiotherapy Quality Assurance (RT-QA)**

The purpose of the RT-QA protocol is to ensure uniformity of all radiotherapy data for all patients.

The working group for radiotherapy quality assurance (RT-QA group) consists of all panel members for radiotherapy and radiotherapy quality assurance. Radiotherapy related treatment information and other relevant documentation for each patient shall be sent to the RT-QA group at least 5 working days before treatment start. Positive or negative feedback shall be provided by the RT-QA group at least 2 working days before treatment start. Considering the prognosis of early stage SCCGL this study-specific delay is not expected to have a substantial impact on the treatment outcome.

After the treatment of first 2 patients in Arm B (radiotherapy) in each center, an on-site or online monitoring by the RT-QA team will be carried out to perform an offline review of the IGRT of these 2 patients' treatment courses. No further patients in this center will be accrued before the successful completion of the on-site monitoring.

### **8.3.11 Dummy Runs**

A two-step dummy run will be performed before the start of the trial in each participating institution. CT images of a HNSCC patient will be made available to participating centers from the RT-QA group. Delineation of target volumes and OARs according to the study protocol will be performed at each center, as well as a treatment plan according to the study protocol. The first step of the dummy run involves the generation of the volumes and uploading the data to the central database. The contours will be reviewed by the physicians and the physicists of the RT-QA group. In case of major deviations, these will be

communicated back to the institution, and a revised version shall be submitted until no major deviations persist. Followed by the approval of the volumes, the second step involves the generation of the RT plan. It shall use the approved structures and the treatment technique per protocol. The treatment plan shall fulfill the requirements defined in the previous sections of the protocol. A patient-specific pretreatment QA verification for the generated RT plan shall be performed and documented appropriately. In case of major deviations, these will be communicated back to the institution, and a revised version of the treatment plan shall be submitted until no major deviations persist.

In the following circumstances, the RT-QA group may ask the local center to repeat the dummy run process:

- Permanent change of the authorized radiation oncologist (temporary absences due to holidays, health reasons etc. do not count)
- An interval of 1 year without a new study patient treated

#### **8.4 Compliance with study intervention**

The compliance with the study interventions will be assured via regular data monitoring and on-site monitoring, which will be coordinated by the CTU Bern, and via individual patient checks and data-flow as mentioned in the previous sections above.

#### **8.5 Data Collection and Follow-up for withdrawn participants**

Participants withdrawn from the trial before any treatment will undergo surgery or radiotherapy as planned by the tumor board. Patients may change their mind and prefer a treatment other than the study arm they were randomized to, or no treatment at all.

If a patient is withdrawn during or after the commencement of any study treatment, he/she will be asked, whether their study-specific data collected so far may be used. The data will be anonymized after the analysis.

A patient may also be withdrawn from the study by the local principal investigator, if the patient's participation in the study deemed to bear any additional risk for the well-being of the participant.

#### **8.6 Trial specific preventive measures**

None except for the preventive measures against pregnancy as mentioned under the eligibility criteria and the pregnancy test before the recruitment (and until the end of 3 months after treatment in case of suspicion for pregnancy). During the treatment and within the first 30 days of the follow-up phase, patients have to take contraceptive measures against pregnancy. Effective contraceptives can be hormonal (e.g. contraceptive pill, injections, or implants) or mechanical (e.g. condom, intrauterine pessary, diaphragm, cervical cap or another device). When using mechanical contraceptives, two methods of mechanical contraception have to be used. When using hormonal contraceptives, one additional method of mechanical contraception has to be used.

#### **8.7 Concomitant Interventions (treatments)**

No study-specific concomitant interventions are planned. However, symptom-oriented medications are allowed (e.g. pain medications to alleviate post-operative pain, steroids to alleviate laryngeal edema during radiotherapy).

## 9. STUDY ASSESSMENTS

### 9.1 Study flow charts

**Table 1: Summary flowchart**

| Study Periods →                                                                             | Screening and Enrollment                                     | Treatment Period                                                                               | Follow-up until 60 months after enrollment                                                                                                   |
|---------------------------------------------------------------------------------------------|--------------------------------------------------------------|------------------------------------------------------------------------------------------------|----------------------------------------------------------------------------------------------------------------------------------------------|
| Time unit →                                                                                 | Days                                                         | Weeks                                                                                          | Months                                                                                                                                       |
| Patient Information and Informed Consent                                                    | -28 – 0                                                      |                                                                                                |                                                                                                                                              |
| Medical history and demographics                                                            | -28 – 0                                                      |                                                                                                |                                                                                                                                              |
| Panendoscopy, assessment of exposure and staging according to institutional local standards | -28 – 0                                                      |                                                                                                |                                                                                                                                              |
| Eligibility Criteria Check                                                                  | -28 – 0                                                      |                                                                                                |                                                                                                                                              |
| SCCGL-oriented physical examination                                                         | -28 – 0                                                      |                                                                                                |                                                                                                                                              |
| VHI # , RBH, GNE, SPR, JS                                                        | -28 – 0                                                      |                                                                                                | (1.5) # , 6, 12, 18, 24 (+/-15 days)                                                                                              |
| Enrollment and randomization*                                                               | 0                                                            |                                                                                                |                                                                                                                                              |
| Endoscopic assessment of the index tumor, symptom oriented physical examination             | -28 – 0                                                      |                                                                                                | every 3 months (+/-15 days) until 24 th month
every 6 months (+/-15 days) between 24 th and 60 th months |
| Evaluation of actual smoking status and toxicity according to CTCAE v.5.0 (Appendix A)      | -28 – 0 (baseline smoking status and toxicity ‡ ) | weekly during radiotherapy and within one week of surgery: no need to document except for SAEs |                                                                                                                                              |
| Pregnancy test for women with child-bearing potential                                       | -28 – 0                                                      | 3 – 7 ‡                                                                             | until 3 rd month ‡                                                                                                     |
| Arm A: Transoral CO 2 -Laser Microsurgical Cordectomy ▽               |                                                              | day of surgery +/- day of re-resection                                                         |                                                                                                                                              |
| Arm B: Single Vocal Cord Irradiation ▽                                           |                                                              | 3 (16 fractions)                                                                               |                                                                                                                                              |

GNE: Glottal-to-Noise Excitation Ratio; JS: Jitter and Shimmer; RBH: Roughness – Breathiness – Hoarseness; SAEs: serious adverse events; SCCGL: squamous cell carcinoma of glottic larynx; SPR: Singing Power Ratio; VHI: voice handicap index

\*: Even if done on the same day, patient enrollment shall be done after the completion of the necessary documentation

#: VHI at 6 weeks after the end of treatment (regardless of study arm) will be assessed to evaluate the need for phoniatric rehabilitation, but not as a study-specific outcome measure (i.e. primary endpoint) to avoid lead time bias. Patients with a VHI > 14 will be recommended to undergo a phoniatric rehabilitation, but the examiner should not try to persuade the patient. Similarly, any VHI >14 at any follow-up time point or patients' request justifies the need for phoniatric rehabilitation, which will be recommended to the patients regardless of study arm. No need to record the VHI in the CRFs.

‡: The baseline toxicity scores and smoking status may be documented after the accrual but it must be done before the start of trial treatment.

‡: If clinically indicated

▽: The treatment shall start within 28 days post-accrual

### 9.2 Assessments of outcomes

The time points of each assessment are provided in the summary flow-charts above.

### 9.2.1 Assessment of primary outcome

The VHI allows the person in question to make a subjective assessment of their own vocal problem. It is a questionnaire with 30 items (will be provided in different languages apart from the protocol). Using this questionnaire, the affected people can describe the degree to which their voice restricts their everyday life. The higher the score (0-120), the greater is their subjectively experienced handicap (score 0-14 = no; 15-28 = mild; 29-50 = moderate; 51-120 = severe handicap). The freeware open-source software DigitalVHI by Christian Herbst will be used to record the VHI by each visit. DigitalVHI only generates pdf reports per VHI assessments and does not store any data locally or on a server.

### 9.2.2 Assessment of secondary outcomes

- Perceptual impression of the voice via **Roughness – Breathiness – Hoarseness (RBH)**: The perceptual impression of a vocal signal remains the gold standard in phoniatric diagnosis. By means of reading the phonetically balanced text “The Rainbow Passage” in English and “Die Sonne und der Wind” in German, French and Italian (versions in different languages provided in Appendix C), the speaking voice is assessed by the investigator according to the parameters roughness – breathiness – hoarseness (RBH), using the scale of 0: normal, 1: mild, 2: moderate, 3: severe. In this study, the assessment will be carried out blind.

**Quantitative characteristics of voice** by means of;

- **Jitter and shimmer (JS)** are regarded as objective, quantitative characteristics of voice quality. They describe the variations in the fundamental note of a vocal signal. Jitter is the variation of the cycle-to-cycle frequency in held vowels (in Hz or. %, norm = 0-3%), shimmer is the cycle-to-cycle variation in the amplitude of held vowels (in dB, or. %, norm = 0-20%). In this study, the assessment will be carried out blind.
- **Glottal-to-Noise Excitation Ratio (GNE)** serves to describe the relationship of the voice signal to the noise signal (norm = 1-0) and is also a quantitative characteristic of voice quality. Jitter, shimmer and GNE correspond to the perceptual characteristics roughness – breathiness – hoarseness. In order to carry out JS and GNE, the test subjects hold the vowel /a/ *mezzoforte* for at least 5 seconds at their average speaking pitch. The vocal samples will be recorded and subsequently evaluated using the open source freeware software Praat (<http://www.fon.hum.uva.nl/praat/> by Paul Boersma and David Weenink - Phonetic Sciences, University of Amsterdam [name], Netherlands). In this study, the assessment will be carried out blind.
- **Singing Power Ratio (SPR)**: The ‘brilliant’ sound of a voice is characterized in acoustic terms by a high degree of acoustic energy above 2 kHz. This can be calculated with the aid of the SPR. In the Fast-Fourier-Transformation, the amplitudes of the highest peaks between 2 and 4 kHz and of the highest peaks between 0 and 2 kHz are determined using a vocal sample and the one subtracted from the other. The lower the SPR, the more “sonorous” is the voice. For this, the test subjects hold the vowel /a/ *mezzoforte* for at least 5 seconds at their average speaking pitch. The vocal samples will be recorded and subsequently evaluated using Praat. In this study, the assessment will be carried out blind.

### Toxicity and Oncological Endpoints

- **Loco-regional control** of SCCGL: Loco-regional control is defined as the time between randomization and biopsy-proven HNSCC recurrence at the head and neck region. Patients without any loco-regional failure until the cut-off point will be censored at the last assessment date.
- **Treatment toxicity** at 2 and 5 years based on CTCAE v.5.0. The list of possible treatment-associated toxicities is provided in the Appendix A. Patients will not be further assessed for toxicity in case of a loco-regional and/or distant tumor recurrence.

### 9.2.3 Assessment of safety outcomes

Although the safety endpoints will be reported only at two time points (2 and 5 years), the toxicity will be systematically assessed during and after the treatment in a more frequent schedule: during the treatment, every 3 months until 24 months, and every 6 months between the 24th and 60th months. CTCAE v.5.0 will be used for the documentation of possible toxicities listed in Appendix A.

Adverse events (AE) of grades 1 to 2 (CTCAE v.5.0) between the recruitment and before the 6th month visit do not need to be reported in the study-specific documents and will be managed according to institutional local standards. Any AE of grade 3 and above is considered as a serious adverse event

(SAE) and shall be reported according to Section 10.

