### 8.2.5 Expected Complications / Surgical Adverse Events of TLM

In this study, surgical complications will be noticed within 30 days after primary and also re-resection TLM. Day 0 is the date of surgery.

Complications at the primary site after TLM are generally rare, but the most common ones consist of:

- Post-operative bleeding
- Airway compromise

Other known and common complications of any surgery include:

- Complications related to general anesthesia
- Pain
- Wound site infection
- Thromboembolic events
- Pneumonia
- Single or multi-organ failure

Surgical Adverse Events will be recorded using the Clavien-Dindo classification of surgical complications (Appendix B). Serious adverse events (SAE) will be documented reported via SAE procedure (Section 10).

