## 10. SAFETY

An Adverse Event (**AE**) is any untoward medical occurrence in a patient or a clinical investigation subject which does not necessarily have a causal relationship with the trial procedure. An AE can therefore be any unfavorable or unintended finding, symptom, or disease temporally associated with a trial procedure, whether or not related to it.

**Severity:** The term “severe” is often used to describe the intensity (severity) of a specific event (as in mild, moderate or severe, or as described in CTCAE v.5.0 grades); the event itself, however, may be of relative minor medical significance (such as severe headache). This is not the same as “serious,” which is based on patient/event outcome or action criteria usually associated with events that pose a threat to patient’s life or functioning. Seriousness (not severity) serves as a guide for defining regulatory reporting obligations.

**SAE:** A **Serious Adverse Event** is defined as any untoward medical occurrence or effect in a patient, whether or not considered related to the protocol treatment, that:

- results in death;
- is life-threatening (i.e. an event in which the subject was at risk of death at the time of event; it does not refer to an event which hypothetically might have caused death if it was more severe);
- requires inpatient hospitalization or prolongation of existing patient hospitalization;
- results in persistent or significant disability or incapacity;
- is a congenital anomaly or birth defect;
- is a medically important event or reaction.

Medical and scientific judgment should be exercised in deciding whether other situations should be considered serious such as important medical events that might not be immediately life-threatening or result in death or hospitalization but might jeopardize the patient or might require intervention to prevent one of the other outcomes listed in the definition above.

**Inpatient hospitalization:** a hospital stay equal to, or greater than, 24 hours.

**Second primary malignancy** is one unrelated to the treatment of a previous malignancy (and is not a metastasis from the previous malignancy).

**Secondary malignancy** is a cancer caused by treatment for a previous malignancy (e.g., treatment with investigational agent/intervention, radiation or chemotherapy). A secondary malignancy is not considered a metastasis of the previous malignancy.

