| Dysphagia           | Symptomatic, able to eat regular diet                                                                  | Symptomatic and altered eating/swallowing                                                                                                       | Severely altered eating/swallowing; tube feeding or total parenteral nutrition or hospitalization indicated            | Life-threatening consequences; urgent intervention indicated                                        |
| Hoarseness          | Mild or intermittent voice change; fully understandable; self-resolves                                 | Moderate or persistent voice changes; may require occasional repetition but understandable on telephone; medical evaluation indicated           | Severe voice changes including predominantly whispered speech                                                          | -                                                                                                   |
| Laryngeal Stenosis  | Asymptomatic; clinical or diagnostic observations only; intervention not indicated                     | Symptomatic (e.g., noisy airway breathing), no respiratory distress; medical intervention indicated (e.g., steroids); limiting instrumental ADL | Limiting self-care ADL; stridor; endoscopic intervention indicated (e.g., stent, laser)                                | Life-threatening consequences; urgent intervention indicated                                        |
| Pharyngeal Stenosis | Asymptomatic; clinical or diagnostic observations only; intervention not indicated                     | Symptomatic (e.g., noisy airway breathing), no respiratory distress; medical intervention indicated (e.g., steroids); limiting instrumental ADL | Limiting self-care ADL; stridor; endoscopic intervention indicated (e.g., stent, laser)                                | Life-threatening airway compromise; urgent intervention indicated (e.g., tracheotomy or intubation) |

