| Aspiration          | Asymptomatic; clinical or diagnostic observations only; intervention not indicated                     | Altered eating habits; coughing or choking episodes after eating or swallowing; medical intervention indicated (e.g., suction or oxygen)        | Dyspnea and pneumonia symptoms (e.g., aspiration pneumonia); hospitalization indicated; unable to aliment orally       | Life-threatening respiratory or hemodynamic compromise; intubation or urgent intervention indicated |
| Pain                | Mild pain                                                                                              | Moderate pain limiting instrumental ADL                                                                                                         | Severe pain limiting self-care ADL                                                                                     | -                                                                                                   |
| Hypothyroidism      | Asymptomatic; clinical or diagnostic                                                                   | Symptomatic; thyroid replacement                                                                                                                | Severe symptoms; limiting self-care                                                                                    | Life-threatening consequences;                                                                      |

|                                          |                                                              |                                                               |                                                             |                                                                       |
|------------------------------------------|--------------------------------------------------------------|---------------------------------------------------------------|-------------------------------------------------------------|-----------------------------------------------------------------------|
|                                          | observations only;
intervention not
indicated          | indicated; limiting
instrumental ADL                       | ADL; hospitalization
indicated                           | urgent intervention
indicated                                      |

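### Section 9.2.3 makes every grade 3 or higher AE an SAE, Section 10 separates severity from seriousness, and Table 1 lets the choice decide whether a treatment-period grade 3 event is recorded

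*Protocol*

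**What the plan says.** Four places in the protocol bear on this.

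- **Section 9.2.3** sets a grade rule: "Any AE of grade 3 and above is considered as a serious adverse event", to be reported under Section 10. For grades 1 to 2 between recruitment and the month 6 visit, it says that they "do not need to be reported in the study-specific documents and will be managed according to institutional local standards".
- **Section 10** lists the SAE criteria: death, threat to life, hospitalization, disability, congenital anomaly, or a medically important event. No CTCAE grade appears. It distinguishes severe from serious, offers severe headache as a severe event that may matter little medically, and concludes: "Seriousness (not severity) serves as a guide for defining regulatory reporting obligations". Section 10.2 likewise applies CTCAE grading to serious and non-serious AEs alike.
- **Table 1**, printed in the Study Schedule and again in Section 9.1, gives the treatment-period rule for toxicity: "weekly during radiotherapy and within one week of surgery: no need to document except for SAEs".
- **Section 10.5** requires SAEs to reach the sponsor within 24 hours. Its opening sentence limits this to events caused by a protocol intervention, whereas the list and instructions below it speak of all SAEs.

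Toxicity at 2 and 5 years is a secondary outcome (Section 5.2). Section 5.4 adds that toxicity is assessed systematically during treatment as well. The data are summarized by arm (Section 11.3.2) and compared with the TAME method (Section 11.3.3).

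**The concern.** Two SAE definitions in one protocol would usually mean some over-reporting and little else. Here the definition also acts as a recording rule, because Table 1 makes SAE status the condition for documenting toxicity during treatment. A site that applies Section 10 as written can leave a non-serious grade 3 event out of the study data and still believe that it has complied. A site that applies Section 9.2.3 files the same event within 24 hours and, where a link to the intervention cannot be excluded, it also goes to the ethics committee within 15 days (Section 10.6).

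At stake are the SAE counts and the completeness of grade 3 toxicity in the treatment period. An analysis plan cannot repair the second, since it cannot recover events that were never entered.

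**Working it through.** The protocol states no figure to reproduce here. The check sets the rules side by side and then sizes one patient.

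**Step 1: the test event.** Appendix A grade 3 hoarseness is defined as "Severe voice changes including predominantly whispered speech" and grade 3 pain as "Severe pain limiting self-care ADL". Neither definition by its wording entails death, threat to life, hospitalization or any other Section 10 criterion. An investigator might judge a particular case disabling or medically important, but that is a case-by-case decision. Increased hoarseness is listed in Table 2 as an acute effect of SVCI, so the event type is foreseeable.

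**Step 2: apply both rules to a grade 3 event that meets no Section 10 criterion.**

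| Period | Following Section 9.2.3 | Following Section 10 |
|---|---|---|
| During radiotherapy, or within one week of surgery | SAE, 24-hour report, recorded | Not an SAE; Table 1 requires no documentation |
| After that, up to the month 6 visit | SAE, recorded | Not an SAE, but only grades 1 to 2 are exempt, so not clearly exempt from recording |

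SAE status differs in both rows. Loss of the record is possible only in the first, which covers 16 fractions (about three weeks) in Arm B and one week in Arm A.

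**Step 3: events that are not at issue.** A grade 3 event with hospitalization, threat to life or disability is an SAE under both rules.

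**Step 4: size of one patient.** Section 11.1 plans 17 patients per group, so one patient recorded or not is 1/17 = 5.9 percentage points of an arm's rate.

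**Step 5: how many patients.** The protocol gives no rate. For an assumed rate r of treatment-period grade 3 events meeting no Section 10 criterion, the expected number of such patients in an arm is 17r, and the chance of at least one is 1 − (1 − r)^17:

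| Assumed r | Expected patients (17r) | Chance of at least one |
|---|---|---|
| 2% | 0.34 | 29% |
| 5% | 0.85 | 58% |
| 10% | 1.7 | 83% |
| 20% | 3.4 | 98% |

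These are patients whose classification depends on the rule followed. They would be lost only if treated at sites that follow Section 10. The range runs from probably none to almost certainly some, so the documents do not fix the number.

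**The case against.** The best defence is that Section 9.2.3 is the trial-specific rule and Section 10 gives general definitions. On that view Section 9.2.3 deliberately widens the SAE list, and Table 1 fits it: grades 1 to 2 are left out and grade 3 and above are recorded. The medically important criterion leaves room for this, and a site reading the protocol so loses no grade 3 event. This stands as far as it goes, and it is why the conclusion is that events may go unrecorded, not that they will. It does not remove the conflict. Section 9.2.3 sends the reader to Section 10 for reporting, and Section 10 rejects severity as the guide.

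A reader might infer more than the documents support, in three ways.

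- **That the arms are captured unequally and the comparison is biased.** Section 8.2.5 does say "Surgical Adverse Events will be recorded using the Clavien-Dindo classification of surgical complications", for 30 days and in Arm A only. But the exemption for CTCAE grades 1 to 2 applies to both arms, Clavien-Dindo is not among the outcomes in Section 5, and Sections 11.3.2 and 11.3.3 give it no between-arm analysis. Bias from this source is not shown.
- **That all early grade 3 toxicity is in doubt.** The recording gap is confined to the Table 1 window.
- **That a substantial share of an arm is affected.** No rate in the documents supports this. Section 3.4 describes the risks as minimal, and Table 2 lists mild pain and mild odynophagia.

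**Conclusion.** The inconsistency is real and worth correcting. Sections 9.2.3 and 10 classify the same grade 3 event differently, and in the Table 1 window the classification decides whether it must be recorded. SAE counts and treatment-period grade 3 toxicity can therefore depend on which section a site follows. Each affected patient is worth 5.9 percentage points of an arm's rate at the planned 17 per arm. How many there would be cannot be estimated from the protocol.

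The conclusion rests on two assumptions: that some grade 3 events during treatment meet no Section 10 criterion, and that at least one site reads Section 10 as governing. The VHI primary endpoint and the sample size are unaffected.

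**What to change.** 1. Reconcile Section 9.2.3, Section 10, both printings of Table 1 and the opening sentence of Section 10.5 to a single SAE definition. Which definition is the sponsor's choice. If grade 3 is to confer SAE status, Section 10 must list it; if not, Section 9.2.3 must drop it.
2. Whichever is chosen, require every CTCAE grade 3 or higher event in both arms to be entered in the eCRF from randomization, serious or not. Completeness of the toxicity data then no longer depends on the SAE definition.
3. Widen the exception in Table 1 so that it covers grade 3 or higher events as well as SAEs.

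The cost is a wording amendment and one eCRF entry rule. If the sponsor keeps the Section 10 criteria alone, sites would also file fewer 24-hour forms for non-serious events. No planned analysis needs to change.
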